### Randomization and blinding

Stratified permuted block randomization will be applied to stratify participants into different stratum and blocks (block sizes 4, 4, 2, 6, 2) based on gender and probable confounders including age, BMI, and NAFLD severity. Each block will be randomly allocated to the intervention or control groups. The sequence of the blocks will be prepared for each stratum using a random number table. For each patient in a definite block, a matched person in terms of the aforementioned variables would be considered in that block. Participants and investigators will be blind to the trial group assignments until the end of the study and data analysis, with the exception of the study pharmacist. A randomization list and sequentially numbered drug containers will be provided by the study pharmacist.

### Study interventions

Forty-four eligible NAFLD patients will be randomly allocated to placebo (*n* = 22) and intervention groups (*n* = 22). Naringenin capsules (contain 100 mg naringenin) and identical placebo capsules (contain 100 mg cellulose) will be respectively administered to patients in the intervention and control groups twice a day, before lunch and dinner, for 4 weeks. Naringenin and placebo capsules will be similar in weight, size, shape, taste, color, odor, and lot number. Participants will be informed how to use their supplements, and they will be followed by phone calls once a week. Also, due to ethical considerations, physical activity and dietary recommendations will be provided by the researchers in order to improve participants’ lifestyles in both naringenin and placebo groups. No specialized diet or physical activity plan will be provided for study patients.

### Outcomes

#### Primary and secondary outcomes

The primary outcome of the current research includes alteration in plasma adiponectin concentrations. Alterations in plasma NRG-4 concentrations; lipid profile including triglyceride (TG), high-density lipoprotein cholesterol (HDL-C), low-density lipoprotein cholesterol (LDL-C), and total cholesterol (TC); glycemic parameters including fasting blood sugar (FBS), fasting blood insulin (FBI), hemostatic model assessment of insulin resistance (HOMA-IR), and Quantitative Insulin Sensitivity Check Index (QUICKI); levels of aminotransferases including aspartate aminotransferase (AST) and alanine aminotransferase (ALT); liver steatosis; NFS; weight; BMI; WC; blood pressure; hematological parameters; energy intake; and consumption of energy-contributing nutrients including carbohydrates, fat, and protein are considered as secondary outcomes.

### Measurements and assessments

#### Clinical assessments

Medical history, alcohol consumption, smoking history, and demographic factors including age, sex, race, income level, employment status, education level, marital status, and homeownership will be asked from all the patients at the beginning of the research. Blood pressure will be measured using a mercury sphygmomanometer after at least 5-min resting. The measurement will be performed on two occasions, and the mean of the two will be considered as the individual’s blood pressure.

#### Assessment of physical activity

For estimating the physical activity level of participants, an International Physical Activity Questionnaire-Short Form (IPAQ-SF) which was previously validated in Iran will be applied. The IPAQ form computes and reports physical activity in metabolic equivalents per minute (MET-min) per week. The levels of physical activity will be reported in three categories including low activity, moderate activity, and high activity levels based on the IPAQ scoring protocol [24, 25]. To control confounders, alterations in physical activity levels throughout the study will be taken into consideration for statistical analysis.

#### Nutritional assessments

At the onset and end of the trial, body weight and height will be measured to the nearest 0.1 kg and 0.1 cm using the Seca scale and stadiometer (Seca), respectively. The individuals will be measured when they are barefoot and wearing light clothing. BMI is computed by dividing weight in kilograms by height in meters squared. WC is measured using the middle of the lowest gear, the high point of the iliac crest, and on the biggest environmental gluteal muscle, respectively. A 3-day food record (2 weekdays and 1 weekend day), a valid instrument for the evaluation of diet, will be used for dietary assessment in patients. The 3-day food record will be completed at the beginning and end of the intervention by face-to-face interview. We will analyze the information about dietary consumption by the Nutritionist IV software. To control confounders, alterations in dietary intakes throughout the study will be taken into consideration for statistical analysis.

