**Methods and analysis:**

This is a double-blind, randomized, placebo-controlled clinical study that will investigate the impacts of naringenin supplementation in overweight/obese patients with NAFLD. Liver ultrasonography will be applied to diagnose NAFLD. Forty-four eligible overweight/obese subjects with NAFLD will be selected and randomly assigned to receive naringenin capsules or identical placebo (each capsule contains 100 mg of naringenin or cellulose), twice daily for 4 weeks. Participants will be asked to remain on their usual diet and physical activity. Safety of naringenin supplementation was confirmed by the study pharmacist. The primary outcome of this study is changes in adiponectin circulating levels. The secondary outcomes include changes in NRG-4 levels, liver function indices, metabolic parameters, body weight, body mass index (BMI), waist circumference (WC), blood pressure, and hematological parameters. Statistical analysis will be conducted using the SPSS software (version 25), and *P* value less than 0.05 will be regarded as statistically significant.

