**Discussion:**

We hypothesize that naringenin administration may be useful for treating NAFLD by modulating energy balance, glucose and lipid metabolism, oxidative stress, and inflammation through different mechanisms. The current trial will exhibit the effects of naringenin, whether negative or positive, on NAFLD status.

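### Using on-trial changes in diet and physical activity as confounders can bias the estimate of naringenin's total effect; adjust for baseline covariates only

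*Protocol article*

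**What the plan says.** All places are in the protocol article.

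- *Nutritional assessments*: "To control confounders, alterations in dietary intakes throughout the study will be taken into consideration for statistical analysis". On timing: "The 3-day food record will be completed at the beginning and end of the intervention by face-to-face interview".
- *Assessment of physical activity*: "To control confounders, alterations in physical activity levels throughout the study will be taken into consideration for statistical analysis".
- *Statistical analysis*: ANCOVA is to compare the arms on the primary and secondary outcomes at the end of the trial and to adjust the final results for possible confounders. The section does not list the confounders or restrict them to baseline variables, and it names no baseline-only model as primary.
- *Primary and secondary outcomes*: the primary outcome is the change in plasma adiponectin. Among the rest, "energy intake; and consumption of energy-contributing nutrients including carbohydrates, fat, and protein are considered as secondary outcomes". Physical activity is not in the list.
- *Abstract, Discussion*: the hypothesis is that "naringenin administration may be useful for treating NAFLD by modulating energy balance" and through other pathways.

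**The concern.** A confounder of the treatment comparison must influence, or share a cause with, which arm a patient is in. Randomisation fixes the arm before any on-trial change in eating or activity occurs, so such a change cannot be a confounder. It can, however, be a consequence of treatment. The plan allows for this itself, since it treats intake both as an outcome that naringenin may alter and as a nuisance to be removed.

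The stated objective is the effect of naringenin on adiponectin, which is the total effect. A model that holds on-trial diet and activity constant targets only the part that does not pass through them. If unmeasured factors influence both the change in diet and the outcome, conditioning on diet change can also create an association between arm and outcome where none exists (collider bias). Because ANCOVA is planned for the secondary outcomes too, the problem is not confined to adiponectin. For the intake outcomes, adjusting for change in intake would be circular.

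**Working it through.** **1. The plan's own figure.** *Sample size calculation* gives 21 per group from 90% power, two-sided α = 0.05, and the values 0.99 and 0.93. No standard deviation is given, so 21 cannot be reproduced from the stated inputs. For illustration I solve for the standardised effect d at which a two-sample t test with 21 per group (40 df) has 90% power. The result is d = 1.025 (noncentrality 1.025 × √(21/2) = 3.32). This value is back-solved and does not appear in the plan.

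**2. What adjustment does to the estimate.** Assume one on-trial change M (diet, say), with M and the outcome each having SD 1 within arm. Treatment moves M by a, M moves the outcome with slope b, and a share s of the total effect runs through M.

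- Mediated part: a × b = s × d, so a = s × d / b.
- Estimate without M: d.
- Estimate with M: (1 − s) × d, which is 0.82, 0.72 and 0.51 for s = 20%, 30% and 50%.
- If a = 0, both models estimate the same effect and the bias is zero.

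**3. Power of the adjusted test.** M also explains outcome variance and is correlated with arm, so power does not follow from the smaller effect alone. With n = 21 per group:

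SE ≈ √[(1 − b²) × (2/n + (a² + 2/n)/(2n − 4))], and the test has 2n − 3 = 39 df.

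Worked cell, s = 30% and b = 0.5: a = 0.3 × 1.025 / 0.5 = 0.615; SE = √[0.75 × (0.0952 + 0.473/38)] = 0.284; noncentrality 0.718/0.284 = 2.53; power 0.69.

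| Share mediated | Adjusted effect | b = 0.3 | b = 0.5 | b = 0.7 |
|---|---|---|---|---|
| 20% | 0.82 | 0.72 | 0.82 | 0.94 |
| 30% | 0.72 | 0.55 | 0.69 | 0.86 |
| 50% | 0.51 | 0.24 | 0.37 | 0.55 |

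Simulation agrees to about 0.01. The ranges are therefore about 0.71-0.94, 0.55-0.86 and 0.24-0.56, against 0.90 without M.

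**4. Collider bias.** Assume no true effect, and an unmeasured factor that loads 0.5 on both diet change and outcome. The within-arm slope of outcome on diet change is then 0.5 × 0.5 = 0.25, and the adjusted estimate is −0.25 × a. If treatment moves diet by 0.5 or 0.8 SD, this is −0.13 or −0.20 SD. In simulation with 22 per arm, the type I error was 0.07 and 0.10 instead of 0.05. Opposite signs for the loadings or for a would turn the direction round.

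The values of s, b, a and the loadings are all assumptions.

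**The case against.** The strongest reply is that the harm is conditional. Bias for the total effect needs naringenin to move diet or activity, and the article's evidence for that is thin. Elsewhere it explains the energy pathway by energy homeostasis, fatty acid oxidation and reduced adipogenesis, not by lower intake. It nowhere says that naringenin alters activity. With s = 50%, the assumed slopes require a shift of 0.7 to 1.7 SD in M within four weeks, which nothing in the document supports. All this stands, and it limits what can be said about size.

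Two replies on wording stand in part. The article says that the changes will be considered, not that they enter the model as covariates, and an analysis plan that is not shown may say more. But their declared purpose is to control confounders, and ANCOVA is the method named for that, so little other reading is left. The statistical section also lists simple two-group tests, but it names none as primary and ties the final results to the ANCOVA.

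A reader might go further in three ways that the documents do not support:

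- *Collinearity.* It is tempting to add that energy and its three macronutrients would make the model unstable. No section puts all four in one model. Collinearity among covariates also inflates the errors of their own coefficients, not by itself that of treatment. In simulation with four covariates unrelated to arm and outcome, the SD of the treatment estimate was 0.33 at every correlation from 0 to 0.999.
- *A single power figure.* Shrinking d in a plain t test gives 74%, 62% and 37% for the three shares. That is not the planned test. In the ANCOVA, power at 20% mediation can even exceed 90%.
- *The lifestyle advice.* *Study interventions* says that "physical activity and dietary recommendations will be provided by the researchers in order to improve participants’ lifestyles". This applies to both arms of a double-blind trial, so it is no reason to expect a difference between them.

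**Conclusion.** The plan is wrong as written to treat on-trial changes in diet and activity as confounders. That conclusion rests on the timing of the measurements and the list of outcomes, and needs no numerical assumption.

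The consequence is that adjustment can bias the estimate of the total naringenin effect. A reader might infer that the estimate is certainly biased, but the documents do not show that. If treatment moves neither diet nor activity the bias is zero, and otherwise its size and direction cannot be found from the document. Under a one-mediator model the estimate falls by exactly the mediated share. The power ranges illustrate this for a back-solved d of 1.025 and assumed slopes, and do not predict what will happen in this trial.

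There is also a separate inconsistency. The abstract states "Participants will be asked to remain on their usual diet and physical activity", while *Study interventions* provides lifestyle recommendations meant to improve habits, though no specialised plan. This does not establish the present point, but the two statements should be reconciled.

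**What to change.** - In *Nutritional assessments* and *Assessment of physical activity*, delete the statements that on-trial changes will be used to control confounders.
- In *Statistical analysis*, state that the ANCOVAs for the primary and secondary outcomes adjust for baseline covariates only: the baseline value of the outcome and the stratification factors (gender, age, BMI and NAFLD severity).
- Report changes in dietary intake and physical activity by arm. Label any model that adjusts for those changes exploratory, and say that it does not estimate the total effect.
- Separately, reconcile the abstract and *Study interventions* on diet and activity during the trial.

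The cost is wording only. No additional data, visits or patients are needed, and the planned food records and activity questionnaires are still used.

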#### Biochemical measurements

Blood samples (10 ml) will be drawn following a 12-h overnight fasting and centrifuge at 3000 rpm for 5 min to extract serum samples pre- and post-intervention. Complete blood count and serum albumin will be assessed from the whole blood that was placed in EDTA tubes using Hematology Analyzer (Nihon Kohden Celltac alpha MEK-6510) and chromatography method, respectively. The concentrations of TC, TG, LDL-C, HDL-C, and liver transaminases including AST and ALT will be evaluated instantly on fresh blood samples using commercial kits (Pars Azmoon Inc. kit, Tehran, Iran) before and after the intervention. The concentrations of FBI and FBS will be measured using commercial enzyme-linked immunosorbent assay (ELISA) kit (IBT, USA) and glucose oxidase method, respectively. Serum adiponectin and NRG-4 levels will be assessed using ELISA kits (Human Adiponectin and NRG-4 ELISA kits, Crystal Day Bio-Tec, Shanghai, China) pre- and post-intervention. The following formulas will be used to determine QUICKI and HOMA-IR indexes.
$$ \mathrm{QUICKI}:1/\left(\log\ \left(\mathrm{fasting}\ \mathrm{insulin}\ \upmu \mathrm{U}/\mathrm{ml}\right)+\log\ \left(\mathrm{fasting}\ \mathrm{glucose}\ \mathrm{mg}/\mathrm{dl}\right)\right) $$$$ \mathrm{HOMA}-\mathrm{IR}:\left[\mathrm{fasting}\ \mathrm{insulin}\ \left(\upmu \mathrm{IU}/\mathrm{ml}\right)\times \mathrm{fasting}\ \mathrm{glucose}\ \left(\mathrm{mg}/\mathrm{dl}\right)\right]/405 $$

#### Hepatic steatosis and fibrosis assessment

The severity of fatty liver will be evaluated using ultrasonography by an expert radiologist. The presence of fatty liver will be determined in a qualitative manner based on accepted criteria including a diffuse hyper-echoic texture as mild, increased liver echotexture compared to the renal cortex as moderate, and vascular blurring and deep attenuation as severe. Also, the following formulas will be used to determine NAS and FIB-4 indexes. Regarding the NAS index, patients will be classified as low, intermediate, or high probability of fibrosis according to a score < − 1.445, − 1.445 ≤ score ≤ 0.676, and score > 0.676, respectively [26]. Regarding the FIB-4 index, a value of < 1.30 will be considered as a low probability of fibrosis, a value of > 2.67 will be considered as a high probability of fibrosis, and values between 1.30 and 2.67 will be considered as an indeterminate probability of fibrosis [27].
$$ \mathrm{NAS}:-1.675+0.037\times \mathrm{age}\ \left(\mathrm{years}\right)+0.094\times \mathrm{body}\ \mathrm{mass}\ \mathrm{index}\ \left(\mathrm{kg}/{\mathrm{m}}^2\right)+1.13\times \mathrm{impaired}\ \mathrm{fasting}\ \mathrm{glucose}/\mathrm{diabetes}\ \left(\mathrm{yes}=1,\mathrm{no}=0\right)+0.99\times \mathrm{AST}/\mathrm{ALT}\ \mathrm{ratio}-0.013\times \mathrm{platelet}\ \left(\times {10}^9/\mathrm{l}\right)-0.66\times \mathrm{albumin}\ \left(\mathrm{g}/\mathrm{dl}\right) $$$$ \mathrm{FIB}-4:\mathrm{age}\ \left(\mathrm{years}\right)\times \mathrm{AST}\ \left(\mathrm{IU}/\mathrm{l}\right)/\left(\mathrm{platelet}\ \mathrm{count}\ \left({10}^9/\mathrm{l}\right)\times \surd \mathrm{ALT}\ \left(\mathrm{IU}/\mathrm{l}\right)\right) $$

### Sample size calculation

By consideration of a type I error of 5% (*α* = 0.05), a power of 90%, assumptions in the control group of 0.99, and the expected treatment effects of 0.93, according to the mean plasma levels of adiponectin as a primary outcome [28], the sample size was computed to be 21 for each group based on the two-sided *t* test. To compensate for an approximate drop-out rate of 5% during the study period, we elevate the final sample size to 22 subjects in each group.

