## Introduction

Non-alcoholic fatty liver disease (NAFLD), defined as the accumulation of triglycerides within hepatocytes that exceeds 5% of liver weight, is an umbrella word for a broad spectrum of liver abnormalities including non-alcoholic steatohepatitis (NASH), advanced *fibrosis*, cirrhosis, and hepatocellular carcinoma (HCC) [1, 2]. Based on epidemiological evidence, the current global prevalence rate of NAFLD is 25% [3]. Different kinds of methods including platelet count, serum aminotransferase levels, the fibrosis-4 (FIB-4) index, NAFLD fibrosis score (NAS), imaging techniques, ultrasonography, and liver biopsy are used for the diagnosis of NAFLD. Despite the invasive nature of liver biopsy, it remains the gold standard to define and diagnose the severity of NAFLD [4]. However, ultrasonography can determine moderate and severe liver steatosis with an acceptable accuracy. A meta-analysis performed by Hernaez et al. [5] reported that sensitivity and specificity of ultrasonography were 84/8% and 93/6%, respectively. Experts are currently ongoing to rename NAFLD as metabolic-associated fatty liver disease (MAFLD) because of the close relationship between fatty liver and metabolic disorders [6]. Emerging evidence suggests that there is a bidirectional association between NAFLD and its risk factors including obesity, insulin resistance, dyslipidemia, oxidative stress, and inflammation [7]. Adipose tissue secretes a wide variety of bioactive substances, known as adipokines, which dysregulated secretion of these factors is involved in the development of NAFLD. Adiponectin and neuregulins are proposed to be linked with NAFLD [8]. Adiponectin, as an anti-inflammatory adipokine, is known to be inversely associated with insulin resistance, lipid accumulation, and NAFLD by playing a pivotal role in the modulation of hepatic glucose and lipid metabolism, stimulating the AMP-activated protein kinase (AMPK) signaling pathway, and decreasing the expression of peroxisome proliferator-activated receptor-α (PPAR-α) in the liver [9]. Regarding neuregulin-4 (NRG-4), a novel brown adipose tissue (BAT)-secreted adipokine, a growing body of evidence has demonstrated that it may protect metabolic hemostasis by regulating glucose and lipid metabolism. Also, hepatic de novo lipogenesis was controlled by BAT through NRG-4 [10]. In addition, NRG-4 transgenic mice had less lipid accumulation in the liver compared to the control mice [11].

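### The 21 per group and 90% power for adiponectin cannot be reproduced from the printed inputs (0.99 and 0.93, unlabelled, with no SD or unit)

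*Protocol article*

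**What the plan says.** The Sample size calculation section of the protocol article sets alpha at 5% and power at 90%, takes "assumptions in the control group of 0.99, and the expected treatment effects of 0.93, according to the mean plasma levels of adiponectin" from a cited study, and concludes that "the sample size was computed to be 21 for each group based on the two-sided *t* test". It then allows for about 5% drop-out and arrives at 22 per group, 44 in total.

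No SD, no unit and no explicit difference between groups is printed. The section does not say whether the two figures refer to end-of-trial values or to change from baseline; the Outcomes section defines the primary outcome as the alteration in plasma adiponectin.

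On direction, the Introduction says: "Adiponectin, as an anti-inflammatory adipokine, is known to be inversely associated with insulin resistance, lipid accumulation, and NAFLD". A favourable effect would therefore be an increase.

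**The concern.** The size of a two-sample t test depends on the ratio of the expected difference to the SD. The section prints two numbers without saying what either one is, so that ratio has to be guessed. When the guesses that respect the printed labels are tried, none returns 21 from the printed numbers alone.

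This goes beyond detail that a journal article leaves to a fuller document. The article prints a calculation for the primary outcome, inputs and result together, and the result does not follow from the inputs. What is at stake is the stated 90% power: a reader cannot tell which difference in adiponectin, in its own units, the trial was sized to detect.

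**Working it through.** **Inputs from the Sample size calculation section.** Alpha 0.05, two-sided; power 0.90; t test; 0.99 for the control group; 0.93 for the treatment effect; stated result 21 per group. The SD is not given.

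**Formulas.** Normal approximation: n per group = 2 × (1.960 + 1.282)² × (SD/difference)² = 21.01/d², where d = difference/SD. The t-test results use the non-central t distribution with 2n − 2 degrees of freedom and non-centrality d × √(n/2).

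**What 21 per group requires.** Solving for d at n = 21 and 90% power gives d = 1.00 (normal approximation) or 1.025 (t test). The printed inputs would have to yield a standardised difference of about 1.

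**Readings that keep the printed labels and the two-sided test**

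| Reading | d | n per group, normal / t test | Power at 21 (t test) |
|---|---|---|---|
| Difference 0.93, SD 0.99 | 0.93/0.99 = 0.939 | 24 / 25 | 84% |
| Standardised effect 0.93 | 0.93 | 25 / 26 | 84% |
| Arm means 0.99 and 0.93 | 0.06/SD, SD unstated | not computable | not computable |

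On the third reading, 21 per group needs SD = 0.06/1.025 = 0.0585, about 6% of the mean. On this reading only, the treated mean lies below the control mean, which is the unfavourable direction according to the Introduction.

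**Ways of reaching about 21, and what each one adds or changes**

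- Arm means with an SD near 0.06: adds an SD that is not printed.
- Both figures as arm SDs: the pooled SD is √((0.99² + 0.93²)/2) = 0.960. A difference of 1 gives d = 1/0.960 = 1.041, n = 21 and 91% power. This adds the difference itself, which is not printed.
- A one-sided test with d = 0.939 or 0.93: t test n = 21. This contradicts the section, which says "based on the two-sided" t test.
- Labels swapped (difference 0.99, SD 0.93): d = 1.065, t test n = 20, power at 21 is 92%. This reverses the printed roles.
- 0.99 as a standardised effect: 22 (normal) or 23 (t test). This takes the control-group figure as the effect and ignores 0.93.

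**What 21 evaluable patients per group provide, whatever the inputs mean** (two-sided t test): 90% power at 1.03 SD, 72% at 0.8 SD, 35% at 0.5 SD.

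**The case against.** The strongest reply is that nothing here demonstrates a miscalculation. Without an SD, the two-means reading allows no sample size at all, so the inputs cannot be said to contradict 21. The SD, unit and scale may be given in the cited study or in a full protocol that is not shown. On some readings the claim is met or nearly met: 92% power with the labels swapped, 91% with both figures as SDs and a difference of 1, and 84% with difference 0.93 and SD 0.99. The planned comparison is also an ANCOVA, so t-test power is not exactly the power of the final analysis. This stands as far as it goes: 21 is unverifiable, not shown to be false. It does not rescue the paragraph, because each route to 90% brings in a number that is not printed or changes something that is.

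Three stronger conclusions are tempting, and the document does not support them.

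- A reader might infer that the trial was sized for a harmful effect, since 0.93 is below 0.99. That holds only if both figures are arm means. The phrase "according to the mean plasma levels of adiponectin as a primary outcome" may merely name the outcome, and "the expected treatment effects of 0.93" can equally denote a difference. A two-sided test also gives the same n for either sign.
- A reader might assume an SD of 0.1, 0.2 or 0.3 for a difference of 0.06 and find t-test power of 48%, 16% or 10% at 21 per group. Those SDs appear nowhere in the document, so the figures illustrate one reading and do not describe the trial's power.
- A reader might infer that a null result could not be interpreted. It can be, from the estimate and its confidence interval, and the detectable difference in SD units is known. What is missing is its translation into adiponectin units.

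**Conclusion.** The point holds as a failure to reproduce. The label-consistent readings that can be computed give 25 or 26 per group by t test (24 or 25 by normal approximation) against the stated 21, and about 84% power against the stated 90%. The remaining label-consistent reading cannot be computed without an SD.

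This rests on a two-sided alpha of 0.05, equal groups, 21 evaluable patients per group and an unadjusted two-sample t test, all as the section describes. It is worth correcting because it is the only power statement for the primary outcome.

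**What to change.** Rewrite the Sample size calculation paragraph so that it:

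1. says what 0.99 and 0.93 each are (mean, SD, difference or standardised effect), with the unit of measurement;
2. gives the SD and the expected difference with its direction;
3. says whether these refer to end-of-trial values or to change from baseline;
4. restates the power that 21 evaluable patients per group give at those inputs;
5. adds the detectable standardised difference: 1.03 SD for 90% power, with 72% at 0.8 SD and 35% at 0.5 SD for context.

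No added enrolment is asked for; by the Trial status section, recruitment was due to be nearly complete by 20 May 2021. The cost is one paragraph and possibly a less favourable stated power: about 84% if the intended inputs were a difference of 0.93 with an SD of 0.99.
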